##### Measuring treatment response

Following completion of the first round of brief interventions (three sessions of Teen Intervene), we will measure youth’s response to treatment. Treatment response will be measured utilizing the Brief Situational Confidence Questionnaire (BSCQ), an eight item self-report measure of one’s level of confidence in resisting urges to use substances in eight situations: unpleasant emotions, physical discomfort, pleasant emotions, testing of control, urges and temptations, conflict with others, social pressures, and pleasant times with others [42]. Individuals rate their confidence in abstaining from substance use in each of the situations on a 0% (*not at all confident*) to 100% (*completely confident*), with higher scores denoting greater confidence in abstaining from substance use. Treatment response will be determined utilizing a cut-off overall mean score of 70% on the BSCQ (i.e., average of 70% confidence in abstaining from using substance use across all eight scenarios), based on results from previous studies utilizing the BSCQ as a measure of symptom improvement [43]. The cutoff of 70% has two advantages: it is the average treatment response expected for this intervention, and it yields (approximately, if the distribution is symmetric) an anticipated equal sample-size split for responders and non-responders for the second randomization. Those with a post-intervention score of 70% or higher will be considered “treatment responders” and those whose BSCQ post-intervention score is lower than 70% will be considered “treatment non-responders.” Those youth who are considered “responders” will be told that they have successfully completed the intervention; they will complete additional post-treatment measures at 3 and 6 month follow-up. Non-responders will continue to the second randomization.

Following completion of treatment response measures using the BSCQ, those who are identified as “non-responders” (i.e., mean post-test BSCQ score lower than 70) will complete a second round of brief interventions. If youth continue to not respond, clinicians will make recommendations and referrals as appropriate. Following completion of the second round of brief intervention, treatment response will be measured again using the BSCQ and participants will complete 3- and 6- month follow-up (see Fig. 2).

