#### Community partner participants

Community partner participants will be clinicians, case managers, and supervisors working in the CMHC in each county (range n = 10–30). Bachelor’s level case managers from each CMHC site (n = 2 case managers for each county) will be recruited to act as intervention specialists. They will be trained in the brief intervention and provide treatment to YIJJ and their caregivers. Master’s level licensed clinicians from each CMHC (n = 2 for each county) will be trained in the comprehensive substance use intervention and provide treatment to YIJJ.

The juvenile justice system in each county have agreed to participate and implement substance use screening. Designated juvenile probation officers/intake officers will be identified and will be responsible for conducting universal substance use screening with all youth coming through the detention center at intake.

In addition to these primary individuals who will provide interventions, we will seek participation from other personnel (e.g., juvenile justice intake staff, CMHC supervisors) who are involved in the implementation and sustainability of the interventions to complete qualitative interviews and quantitative measures to assess feasibility and implementation in these settings.

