**Fig. 2 Fig2:**
[figure not shown]
Overview of study design. YIJJ who score 1 or more on the CRAFFT will be recruited for the study. If interested and consent to treatment, they will be assessed to determine risk level. YIJJ identified as high-risk youth will be assigned to complete ENCOMPASS. Low to mid risk youth will be assigned to the brief intervention, Teen Intervene. Following the brief intervention, we will measure treatment response using the BSCQ. YIJJ who score below 70% will be considered “non-responders” and referred to ENCOMPASS

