##### Sample size and power

We plan to recruit n = 80 youth and caregiver dyads per county (160 total). We estimate that no more than 10% of youth in each county will be high-risk, resulting in a sample size of n = 16 assigned to ENCOMPASS and n = 144 to first-stage brief intervention (BI). We anticipate 20% loss at 6-month follow-up resulting in n = 12 in the ENCOMPASS group and n = 116 in the first-stage BI with 6 month data (58 responders and 58 non-responders, assuming a 50% response rate. We have accounted for a sample size inflation factor related to potential within-county intraclass correlation (ICC) of outcomes. Specifically, in the first step of the back-calculation, we determined that a sample size of n = 40 per responders and non-responders to the first-stage intervention (with 6-month data) is required under the “independence of observations” assumption (i.e., *before* accounting for clustering) to provide 80% power for the two-sided model-based tests to detect an effect size (0.63) that is between medium (0.50) and large (≥ 0.80). For a first-stage effective sample size of 40 in each group (responder vs. non-responder), there is a 1.39 sample size inflation factor (IF) when the ICC = 0.01 and the number of clusters (i.e., counties) = 2: IF = [1 + (average 40 patients per cluster − 1) × ICC of 0.01]. Therefore, an actual sample size of 56 per first-stage brief intervention (i.e., 40 × 1.39) with 6-month data is required (i.e., an effective sample size of 40 per first-stage brief intervention with 6-month data if observations were not clustered). The sample of 56 in each group will provide adequate power for this feasibility study and its preliminary hypothesis tests, given that we anticipate n = 58 per first-stage group (responder vs. non-responder) with 6-month data. This power calculation is conservative because the longitudinal models will have slightly increased power due to incorporating all available data (baseline, 3-months, 6-months), including data from persons missing one but not all times points. The goal will be to estimate effect sizes, for which the planned sample size will be adequate. A minimum of 12 per group is recommended for estimating effects sizes of continuous outcomes in pilot or feasibility studies [44].

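### The protocol gives incompatible routes for Teen Intervene non-responders (a second brief round, or ENCOMPASS), and the sample-size paragraph fits only the first

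*Protocol article*

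**What the plan says.** All references are to the protocol article.

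- **Measuring treatment response, first paragraph:** youth with a mean BSCQ of 70% or more after three Teen Intervene sessions are responders and have finished treatment. For the rest, "Non-responders will continue to the second randomization".
- **Measuring treatment response, second paragraph:** the same non-responders "will complete a second round of brief interventions". Clinicians make referrals if response is still lacking. The paragraph cites Fig. 2 for this sequence.
- **Fig. 2 caption:** low- to mid-risk youth get Teen Intervene, and those scoring below 70% afterwards are classed as non-responders "and referred to ENCOMPASS". No second brief round or second randomisation appears in the caption.
- **Risk level determination:** low- and mid-risk youth are randomised between Teen Intervene and Family Check-Up. The abstract and the Fig. 2 caption name Teen Intervene alone.
- **Sample size and power:** 16 youth are "assigned to ENCOMPASS and n = 144 to first-stage brief intervention (BI"). The 6-month figures are 12 and 116, the latter split into 58 responders and 58 non-responders.
- **Preliminary analyses:** responders and non-responders are compared on BSCQ and substance use through 6 months. A separate model covers youth assigned to ENCOMPASS.

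**The concern.** The text and the figure that it cites describe the same decision point and give different treatments. One is a further brief intervention from a bachelor's-level case manager. The other is a combined motivational, cognitive-behavioural, contingency-management and medication programme from a licensed clinician. Two sites could follow different routes, and each would comply with the document.

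This bears on the analysis in two ways. First, the responder versus non-responder comparison uses 3- and 6-month outcomes. On the caption route the non-responders' outcomes would partly be outcomes of ENCOMPASS, and on the text route they would not, apart from later referrals. Second, the only ENCOMPASS number in the plan is the one that follows if no non-responder is sent there at that point.

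The second randomisation adds to the confusion. With a single brief intervention, the document offers no alternatives to randomise between. It looks like a remnant of the two-intervention design that still stands under Risk level determination and in Table 1, which lists a Family Check-Up monitoring report and a measurement after a first and second intervention.

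**Working it through.** **Inputs, all from Sample size and power.** Total: "We plan to recruit n = 80 youth and caregiver dyads per county (160 total"). High-risk share: "We estimate that no more than 10% of youth in each county will be high-risk". Loss at 6 months: 20%. First-stage response: 50%.

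**Reproducing the plan's figures.**

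- ENCOMPASS: 0.10 × 160 = 16. Brief intervention: 160 − 16 = 144. Both as stated.
- With 6-month data: 0.8 × 16 = 12.8 (stated 12) and 0.8 × 144 = 115.2 (stated 116). The differences are rounding, and 12 + 116 = 128 = 0.8 × 160.
- Split at 50% response: 116 / 2 = 58 and 58, as stated.

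These figures contain no movement from the brief intervention into ENCOMPASS.

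**Youth affected.** 144 × (1 − 0.5) = 72 non-responders, before any loss to follow-up.

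**Text route (second brief round).** ENCOMPASS stays at 16, or 12 at 6 months, plus an unspecified number of later clinician referrals. This agrees with the sample-size paragraph.

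**Caption route (referral to ENCOMPASS), every referral taken up.**

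- Ever receiving ENCOMPASS: 16 + 72 = 88.
- With 6-month data: 12 + 58 = 70 on the plan's own figures (0.8 × 88 = 70.4).
- Share first classed low or mid risk: 72 / 88 = 82%.

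**Sensitivity to the response rate**, from 16 + 144 × (1 − response rate):

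- 70% response: 16 + 43.2 = 59.2, about 59
- 60% response: 16 + 57.6 = 73.6, about 74
- 50% response: 16 + 72 = 88
- 40% response: 16 + 86.4 = 102.4, about 102
- 30% response: 16 + 100.8 = 116.8, about 117

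**Sensitivity to uptake.** If only half of those referred at 50% response started ENCOMPASS (my assumption), the total would be 16 + 36 = 52.

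**What does not change.** Responder status is fixed by the BSCQ score before the routes diverge. The 58/58 group sizes are therefore the same on either route, and so is the power calculated from them. Responders have finished treatment, so their outcomes are untouched.

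**The case against.** The best defence is that the plan is more coherent than it first looks. A randomisation is an allocation step, not a treatment, and can be read as leading into the second brief round. A reader might count three different destinations for non-responders, but the document supports only two.

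The wording on ENCOMPASS is also fairly consistent. High-risk youth are assigned to it under Risk level determination, in the Fig. 2 caption and under Sample size and power, and the separate model is for those assigned. The caption uses a different verb, referred, for non-responders. So the natural reading of the separate model is the initially high-risk group. Formal analysis-set definitions may also sit in a document that is not shown. This stands: one cannot say that the ENCOMPASS model would mix the two populations, only that a sentence excluding it would help.

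Some stronger inferences also fail:

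- **That the 6-month results are uninterpretable.** Responders' outcomes are unaffected, the group sizes hold, and the section Analyses calls the tests preliminary in a feasibility study.
- **That a stated ENCOMPASS precision is wrong.** None is stated. The section gives only 12 youth and a recommended minimum of 12 per group for estimating effect sizes.
- **That therapist capacity is exceeded.** Community partner participants says that two licensed clinicians per county "will be trained in the comprehensive substance use intervention and provide treatment to YIJJ". No capacity, caseload limit or recruitment period is given to test this against.
- **That ENCOMPASS will treat 88 youth.** That number is conditional on the caption route, 50% response and full uptake.

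None of this removes the conflict between the text and the caption. The feasibility label does not excuse it either: the stated goal is to estimate effect sizes for a larger study, and that needs a defined treatment sequence.

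**Conclusion.** The plan is wrong as written. It gives two incompatible next treatments for Teen Intervene non-responders, about 72 of 144 youth at the assumed 50% response. It also keeps randomisation steps that do not fit a single brief intervention.

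The planned ENCOMPASS numbers of 16, and 12 at 6 months, agree only with the text route. On the caption route with full uptake, up to about 88 youth would ever receive ENCOMPASS, or about 59 to 117 for response rates from 70% to 30%. At 50% response about 70 would have 6-month data. What the non-responders' 3- and 6-month outcomes measure depends on the route.

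The finding goes no further than that. It does not show which route is intended.

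**What to change.** 1. Reconcile Risk level determination, Measuring treatment response, the Fig. 2 caption, Preliminary analyses and Sample size and power to one pathway. This includes whether Family Check-Up and either randomisation remain. The choice of route is for the clinical team.
2. State that youth are analysed by initial assignment. Teen Intervene results include everyone who started it, whatever treatment followed. The separate ENCOMPASS model includes only youth initially classified high-risk. Youth referred to ENCOMPASS later are reported separately.
3. If the caption route stands, give the expected number of referred youth beside the 16, with the assumed response rate and uptake.

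The cost is wording in four sections and one caption. Data Availability says that data collection has not started, so no data would be affected. The required sample size for the responder versus non-responder comparison does not change.

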**Fig. 2 Fig2:**
[figure not shown]
Overview of study design. YIJJ who score 1 or more on the CRAFFT will be recruited for the study. If interested and consent to treatment, they will be assessed to determine risk level. YIJJ identified as high-risk youth will be assigned to complete ENCOMPASS. Low to mid risk youth will be assigned to the brief intervention, Teen Intervene. Following the brief intervention, we will measure treatment response using the BSCQ. YIJJ who score below 70% will be considered “non-responders” and referred to ENCOMPASS

#### Ongoing data collection

In addition to the intervention, participants and their caregivers will complete data collection at three time points: baseline, 3 months, and 6 months. Parents and youth each will be compensated $50 at each data collection point. In addition to measures of treatment response as described above, participants will complete self-report measures of family functioning, mental health symptoms, other risk behaviors, and psychosocial functioning (see Table 1 for overview of measures). These additional measures will help to explore additional characteristics related to treatment response.

Community partners will complete pre- and post-intervention measures related to feasibility of implementation and sustainability (e.g., organizational climate; see Table 1 for complete list of measures).

### Data analysis

#### Measurement of intervention effectiveness and treatment response

##### Preliminary analyses

Preliminary analyses will be used to compare the primary treatment response outcome (confidence of abstaining measured by the BSCQ) and substance use outcome across the responders and non-responders of the brief intervention and ENCOMPASS at baseline, 3 months, and 6 months. A separate model will be utilized to measure effectiveness among those assigned to ENCOMPASS. Substance use will be calculated as number of days in the past month of using alcohol, marijuana, and other substances (range 0–90). These outcomes will be compared between groups with longitudinal generalized linear models (GLM) using the GENMOD procedure with a linear link and normal error distribution. The BSCQ and substance use outcome will be analyzed in separate models. The baseline measure of BSCQ or substance use days will be adjusted as covariates and the repeated measurements of each outcome at 3 months and 6 months will be analyzed simultaneously in the model.

The GLMs are easily fit for non-Gaussian distributions by specifying appropriate link functions and error distributions. If substance use days exhibit sparse counts or large frequency of zeros, we will consider using logistic, Poisson, or zero-inflated Poisson regression models, depending on the observed distributions of outcome behaviors. We also will explore analyzing substance use as time-to-event data using a Cox proportional hazards regression model with the SAS PHREG procedure with censoring if loss to follow-up occurs. Effect sizes will be computed from the model as differences between groups on adjusted means divided by SDs for the linear models, or differences between odds for logistic models or hazards for Poisson models.

The median and relevant percentile (e.g. 25th or 75th) of time to events will be presented by group with associated confidence intervals. All models will include an indicator variable for whether the subject was enrolled as a detained or probation youth. Other covariates will be included based on their theoretical importance as potential confounders and on their imbalance between randomized arms at baseline. We also will examine moderators that we have hypothesized to be potential determinants of treatment response (e.g., family functioning).

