**Methods/design:**

Using a hybrid type 1 clinical effectiveness-implementation design, we will collaborate with CMHCs and juvenile justice in two rural Indiana counties. Guided by the EPIS (exploration, preparation, implementation, sustainability) framework, we will measure factors that affect implementation of substance use screening in juvenile justice and implementation of substance use interventions in CMHCs utilizing self-reports and qualitative interviews with juvenile justice and CMHC staff pre- and post-implementation. YIJJ with mild/moderate substance use will receive a brief interventions and YIJJ with severe substance use will receive ENCOMPASS. We will measure the effectiveness of a brief and comprehensive intervention by assessing changes in substance use across treatment. We anticipate recruiting 160 YIJJ and their caregivers into the study. We will assess intervention outcomes utilizing baseline, 3-, and 6-month assessments.

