### Overview of study design and objectives

In order to address service connection and availability of community-based substance use EBIs for YIJJ, we propose to partner with community mental health centers and juvenile justice systems in two Midwestern counties to: (1) implement universal substance use screening for probation youth (at the point of arrest) to determine substance use risk level and appropriate treatment needed; (2) implement and evaluate the feasibility and effectiveness of a brief substance use intervention for youth with mild/moderate substance use problems in community mental health centers; and (3) implement a comprehensive adolescent-specific evidence-based substance use treatment in community mental health centers. We propose to utilize a hybrid type 1 clinical-effectiveness-implementation trial [37] in order to evaluate facilitators and barriers to implementing this approach as well as test the effectiveness of these interventions in reducing substance use among YIJJ.

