#### Enrollment and baseline assessment

Following initial recruitment, research assistants will complete consent/assent with the caregiver/youth at their home or preferred location. As part of the consent process, participants will be told that this is an intervention study and that they might be assigned to different interventions. Participants and their caregivers also will complete a baseline assessment, which includes self-report measures of demographics, family functioning, mental health, substance use (see Table 1 for overview of all measures).

**Table 1 Tab1:** Overview of data collection

	Informant	Content	Time of Completion
*Implementation measures*			
System-level implementation	CMHC staff, JJ staff, supervisors	Implementation Citizenship Behavior Scale [47], Implementation Climate Scale [48], Implementation Leadership Scale [49], Organizational Readiness to Implement Change (ORIC) [50] Qualitative interviews	Pre-, post-implementation
	JJ staff, supervisors	Qualitative interviews	Pre-, post-implementation
Intervention fidelity monitoring/adherence	Intervention providers	Brief intervention fidelity self-rating checklists ENCOMPASS treatment adherence checklist	Weekly
	Intervention trainers	Fidelity monitoring checklists based on therapist recorded sessions	Monthly
Treatment satisfaction	Parent, youth	Service Satisfaction Scale [51]	1-month post-intervention
Treatment response	Youth	BSCQ [42], FCU Clinical Monitoring Report [43], BSTAD [52]	Post 1st and 2nd intervention
*Participant*-*level measures*			
Demographics	Youth, parent	Family affluence [53], Family characteristics	Baseline
Substance use	Youth	CRAFFT [50], BSCQ [51], BSTAD, AUDIT-C [54]	Baseline, 3-, 6-months
Family functioning	Youth, parent	Parental Monitoring Scale [55]	Baseline, 3-, 6- months
Health service use history	Parent		Baseline, 3-, 6-months
Psychosocial functioning	Youth, parent	Difficulties in Emotion Regulation Scale [56], Peer Conflict Scale [57], Hope & Life Satisfaction Scales [58]	Baseline, 3-, 6-months
Mental health	Youth	K-CAT (computerized child diagnostic evaluation; [59])	Baseline, 6-months

All measures are self-report unless noted otherwise

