##### Analyses

The specific analyses and hypothesis tests (which are preliminary because this is a feasibility study) will assess effectiveness of the brief intervention and ENCOMPASS on substance use outcomes. These data will be used to generate hypotheses about brief and comprehensive interventions for a future larger study.

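### Effectiveness is stated as reduced substance use, but the only outcome called primary, and the sole basis for the responder label, is self-rated confidence on the BSCQ

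*Protocol article*

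**What the plan says.** Three places give the target of the effectiveness evaluation as substance use:

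- Abstract, Methods/design: "We will measure the effectiveness of a brief and comprehensive intervention by assessing changes in substance use across treatment".
- Overview of study design and objectives: the trial will "test the effectiveness of these interventions in reducing substance use among YIJJ".
- Data analysis, Analyses: the hypothesis tests "will assess effectiveness of the brief intervention and ENCOMPASS on substance use outcomes".

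The word primary is attached to something else. Under Preliminary analyses the plan will "compare the primary treatment response outcome (confidence of abstaining measured by the BSCQ) and substance use outcome" across responders and non-responders to the brief intervention and ENCOMPASS.

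Measuring treatment response describes the BSCQ as "an eight item self-report measure of one’s level of confidence in resisting urges to use substances in eight situations". It then sets the rule: "Treatment response will be determined utilizing a cut-off overall mean score of 70% on the BSCQ". The Fig. 2 caption also separates the groups by the BSCQ cut-off alone.

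Preliminary analyses defines substance use as days of use in the past month (range 0 to 90). It gives that outcome a separate longitudinal model with baseline adjustment and names alternatives in case zeros are frequent. It does not say whether this outcome is primary or secondary.

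**The concern.** A plan that asks whether use falls should rank use first. Here the ranking word goes to confidence in resisting urges, and the label that reads as success rests on that confidence alone. Under the rule, a youth who is still using and has a mean BSCQ of 75% is a treatment responder. A youth who has stopped using and scores 65% is a non-responder.

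Two things are at stake. First, the share at or above 70% would naturally be quoted as a response rate and carried into the larger study that the Analyses section says these data will inform, although it says nothing direct about use. Second, comparing BSCQ between groups formed by cutting BSCQ shows a difference whether or not the intervention did anything.

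**Working it through.** **1. Which outcome leads.** Set side by side, the abstract, the objectives and the Analyses section name substance use and do not mention confidence. Preliminary analyses calls BSCQ confidence primary and lists substance use after it, unranked. No other outcome in the article is called primary.

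**2. Whether the sample size settles it.** Inputs from Sample size and power: effect size 0.63, 80% power, two-sided. Alpha is not stated; I assume 0.05.

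- n per group = 2 × (1.960 + 0.842)² / 0.63² = 2 × 7.85 / 0.397 ≈ 39.6, so 40, as stated.
- Inflation factor = 1 + (40 − 1) × 0.01 = 1.39, and 40 × 1.39 = 55.6, so 56, as stated.

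The figures reproduce. The section gives the effect size in SD units without naming an outcome, so it does not show which outcome leads. The present point does not depend on these numbers.

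**3. What the responder rule contains.** It averages eight confidence ratings and compares the mean with 70%. The reasons given for 70% are earlier studies that used the BSCQ as a measure of symptom improvement, the average response expected, and a roughly even split. None is a stated link to actual use in this trial. Table 1 lists the BSTAD under treatment response, after the first and second intervention, and again under substance use, but the rule does not draw on it. Table 1 also files the BSCQ under substance use, which blurs the distinction further.

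**4. The built-in difference on BSCQ.** The groups are formed by cutting the post-intervention BSCQ, and BSCQ is then compared between them at 3 and 6 months. For illustration, assume normal scores and an even split, which the plan expects if the distribution is symmetric.

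- Gap at the moment of labelling = 2 × √(2/π) ≈ 1.60 SD.
- Gap at a later visit whose score correlates r with the labelling score = 1.60 × r.

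| Assumed r | Later gap with no intervention effect (SD) |
|---|---|
| 0.3 | 0.48 |
| 0.4 | 0.64 |
| 0.5 | 0.80 |
| 0.7 | 1.12 |

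The gap equals the 0.63 used for power at r = 0.63 / 1.60 ≈ 0.39. The documents give no value of r. Adjustment for baseline BSCQ should reduce these figures, but it does not remove the gap as long as the labelling score predicts the later score beyond what baseline does.

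**The case against.** The strongest reply is that the text says primary treatment response outcome, not primary outcome. Treatment response is the protocol's own term for the measure taken after a round of brief intervention. The section title names intervention effectiveness and treatment response as two things, and the Analyses section directs the hypothesis tests to substance use. On that reading, confidence leads for response and use leads for effectiveness. This is a possible reading, and the article should have said so. It stays unsettled because nothing else is called primary and substance-use days have no rank.

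A reader might infer that the trial has abandoned use as an outcome. The documents do not support that: use days are defined, baseline-adjusted and modelled separately.

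A reader might also want a count of youths whose label contradicts their use. The documents cannot supply one. They give no BSCQ-use correlation, they anticipate many zeros in use, which makes a bivariate normal calculation unsuitable, and they do not say what level of use would count as response. The label is also assigned after the first round, not to the group with 6-month data.

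Nor can one argue that confidence is easier than use to rate favourably, since Table 1 says all measures are self-report unless noted.

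Two further points stand. The 70% rule is a reasoned choice for steering care, and the tests are preliminary, in a feasibility study. Re-ranking the outcomes also does not turn a comparison of responders with non-responders into a test of the intervention; that is a separate matter.

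**Conclusion.** The point holds as a mismatch between the stated question and the outcome given the primary label, together with a responder label that has no use criterion and a BSCQ comparison that is partly circular. The first two follow from the text alone. The circularity follows from how the groups are formed; only its size is assumed, and it is material (0.48 to 1.12 SD) for r between 0.3 and 0.7 under the assumptions above. It does not follow that use goes unmeasured or that a known number of youths would be mislabelled. Because the study is a feasibility study, the consequence is for what it may conclude and pass on to a larger trial.

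**What to change.** - Name past-month substance-use days, as already defined under Preliminary analyses, as the primary effectiveness outcome, and BSCQ confidence as secondary.
- Report the groups as BSCQ at or above 70% and BSCQ below 70%. Do not present the share at or above 70% as a response rate in substance use, and do not offer the BSCQ difference between these groups as evidence of effectiveness.
- Where the BSTAD collected at the response assessment allows, tabulate BSCQ status against reported use. The article does not give the BSTAD's recall period, so this needs checking first.
- Leave the care pathway triggered by the BSCQ as it is. Separately, reconcile the text of Measuring treatment response, where non-responders receive a second round of brief intervention, with the Fig. 2 caption, where they are referred to ENCOMPASS.

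The cost is protocol wording and one table, with no new data collection planned. The article says data collection has not started, so the change can be made before any outcome is seen. The downside is that use days may show a smaller effect than confidence and may contain many zeros, for which the plan already names alternative models.
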